### Intervention

#### Yoga-add on therapy (YAT: Standard treatment + yoga)

Based on our previous clinical experience the duration of intervention was decided to be 24 weeks^48–51^. Yoga will be offered as an add-on to standard treatment. Participants will be trained in a 40-minute validated yoga module (30 minutes practice+10 minutes relaxation)^48^ during the withdrawal phase and a 60-minute yoga module (45 minutes practice+15 minutes relaxation) during maintenance phase by a trained yoga-instructor (MSc Yoga Science) at the Department of Integrative Medicine, NIMHANS Bengaluru. Table 2 and Table 3 provide the details of the yoga practices to be used during withdrawal and maintenance phase, respectively. Initial supervised training will be conducted for two weeks (five sessions/week). Participants will be asked to join supervised tele-yoga practice from home for the next 22 weeks (at least three days/week). A monthly direct supervised booster session along with yoga-practice booklet, logbook and practice video will be provided. A mobile phone software application will be used to share yoga videos with the participants. Yoga compliance and fidelity to the yoga module (when it has to be done by oneself using video) will also be assessed. Patients will also be monitored by phone calls. Yoga performance will be monitored through the yoga performance assessment scale (YPA).

#### Standard treatment-as-usual (TAU waitlist) group

They will continue to take prescribed medications (OST/MOUD) and psychosocial support as prescribed by the psychiatrist. They will be requested to appear for the planned assessments and will be offered yoga after the six-month study period.

The allocated intervention may be discontinued or modified in case of any subject reporting worsening of symptoms. This data will be documented.

#### Description of some major assessments

**Urine screening for opiods:** Urine screening for opioids is considered as a gold standard for monitoring abstinence. Test depending on the Immunoassay method will be used. It will be done using the opioid strip test which is a rapid, easy and reliable test that is routinely used in clinical settings in India.**Brief Pain Inventory**^57^: It is a reliable and valid tool to assess pain. The scale measures pain intensity, pain severity and pain interference. It has good internal consistency (Cronbach’s alpha = 0.87). The scale is rated by the patient, has 16 items, and provides details regarding pain in the last 24 hours.**Opioid craving scale**^58^: It is a three-item test that is a reliable and valid tool to assess craving in opioid use disorders^59^ and has been used in many studies before. It has good internal consistency (omega = 0.81). Each item is rated by the patient on a visual analog scale from 0–10.**Plasma beta-endorphin estimation:** A blood sample will be collected around 9 am after overnight fasting. 10ml of blood will be drawn and collected into chilled EDTA (1ml/ml of blood) tubes containing aprotinin (500 KIU/ml). The sample will be centrifuged at 1600 × g for 15 minutes at 2 − 8°C. The plasma sample will be immediately frozen and kept at -80°C till analysis. Plasma beta-endorphin levels will be measured using MILLIPLEX MAP multiplex assay kit (Millipore Life sciences, MA), and analyzed by LUMINEX xMAP technology. (CV=6.25%).**Serum Cortisol estimation:** Venous blood (around 5 ml) will be collected from patients in anticoagulant-free tubes around 9 am and serum will be separated after 30 minutes by centrifugation (2900 rpm for 15 minutes). Coded serum sample will be stored at -80°C. The serum cortisol levels will be measured using Enzyme-linked Immuno-Sorbent Assay (ELISA) by commercial reagents according to the manufacturer’s instructions.
**Magnetic Resonance Imaging (MRI):**

##### Data Acquisition

Scans will be executed on a Philips 3T Ingenia CX MRI equipped with a 32-channel proton RF head coil. The cumulative duration for all scanning protocols is estimated to be approximately 50 minutes. Functional imaging will employ a T2*-weighted echo-planar sequence during both resting-state (seven min) and two task paradigms: the Stop-Signal Task (SST, 12 min) and opioid-cue reactivity (12 min).

The whole brain will be covered with axial slices of 3 mm thickness, acquired in descending order (37 slices, 25% gap). Parameters: TR=2000 ms, TE=30 ms, flip angle=78°, matrix=64×64, and FOV=192×192 mm^2^. The first four volumes per run will be discarded. Structural sequences will include T1-(6 min), and T2-weighted (three min). Parameters: T1 − TR/TE (ms) = 6.5/2.9; flip angle = 9°, acquisition matrix = 256×256, and FOV = 256 ×256×192 mm^2^; T2-TR/TE (ms) = 3000/80; flip angle = 90°, acquisition matrix = 240×165, and FOV = 149.5 ×240×176 mm^2^.

##### Resting State fMRI

Participants will be instructed to keep their eyes open, stare at a cross on the screen, and avoid purposeful mental activity during a seven-minute resting-state session. This session is intended to capture intrinsic neural activity patterns in the absence of directed cognitive tasks, allowing for the assessment of various resting-state networks and functional connectivity across brain regions.

##### Task fMRI

Stimuli will be displayed via a plastic mirror mounted on the head coil using E-prime software. **Stop-Signal Task**: Using an event-related design, this task comprises two runs, each with 180 trials over six minutes. Participants will respond to arrows pointing left or right, displayed against a mid-grey background. They are directed to indicate the arrow’s direction as promptly and accurately as possible using a two-button panel aligned with their dominant hand. Notably, 16.67% of these trials are ‘Stop’ trials, wherein an upward arrow unexpectedly appears for 300ms post the directional arrow. The task aims to examine the ability to inhibit responses, facilitated by the higher prevalence of ‘Go’ trials which establish a dominant ‘Go’ response tendency. A dynamic tracking algorithm will adjust the Stop Signal Delay to balance successful and unsuccessful inhibitions at the stop trials, aiming for a 50-50 ratio. This cognitive task will be followed by **Opioid-cue Reactivity task:** This 12-minute task comprises 12 blocks (four neutral (N), four drug-related (D), and four blank (B) blocks) displayed in a pseudo-random sequence. Each block lasts for 30 seconds and features five images shown for six seconds each. Drug-related images are assorted into four sub-categories: tablets, cough syrup, scenes of drug chasing, and intravenous drug use. The task aims to capture neural responses associated with opioid cue-reactivity and quantify alterations in cue reactivity subsequent to intervention.

##### Data Preprocessing and Analysis

The acquired scans will be analyzed using AFNI (Analysis of Functional Neuro Images) software. Preprocessing of T1w and fMRI data will be performed using @SSwarper and afni_proc.py respectively. The @SSwarper command will nonlinearly warp each subject’s T1w anatomical dataset to the India Brain Template (IBT) standard space^60^. Within afni_proc.py, functional data will undergo realignment, slice time correction, co-registration to the T1w image using the LPC+ZZ cost function, spatial warping to IBT space using estimated nonlinear warps and finally spatial smoothing of 6 mm (FWHM) by an isotropic Gaussian Kernel.

For resting-state scans, independent component analysis will be conducted using the GIFT toolbox to segregate neural networks. In the case of the Stop-Signal Task (SST), an event-related design will be implemented to contrast Stop-Success and Stop-Failure conditions, serving as a measure of impulsivity. For the opioid-cue reactivity paradigm, our primary interest lies in the drug-neutral cue contrast.

AFNI’s 3dREMLfit will be utilized to perform generalized least squares (GLSQ) modeling with a restricted maximum likelihood (REML) approach, accounting for temporal correlation. The resulting effect estimates from 3dREMLfit for the contrast conditions from the subject level will subsequently be transferred to the group level via the AFNI program 3dLME. The group will be modelled as a between-subject factor with two levels (TAU and YAT), while time (0, 3, and 6 months) will be treated as a within-subject variable and participants as random factors. A cluster-level family-wise error (FWE) rate corrected significance threshold will be computed to correct for multiple comparisons. This calculation will be undertaken using 3dClustSim, factoring in the smoothness of the residuals, which will be estimated with the -acf option inside the gray matter mask using the 3dFWHMx tool. The thresholds derived will subsequently be applied to the statistical maps produced by 3dLME, aiding in the identification of significant clusters.

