## Plan for research

### Trial design

Single-blinded, randomized, controlled, parallel group superiority trial with a 1:1 allocation ratio.

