### Sample size estimation

For evaluating the primary objectives, the optimal sample size was estimated using the principles and methods for the assessment of primary parameters (abstinence, pain, craving, plasma beta-endorphins and fMRI changes). Based on approximation and estimation from the previous data on the clinical effects of yoga interventions in OUD/other patients with substance use disorder supporting a medium effect size^37,40,43,44^, it was estimated that, for an allocation ratio of one, a sample size of at least 82 OUD patients in each arm (accounting for a potential drop-out rate of 36% at six months^40^ with 60 completing the entire study (for the pre- versus post- comparisons of patients) will be required to detect a two-tailed significant difference of α = 0.01 with an estimated 80% power.

The subset sample size of 50 for imaging studies (in each group − pre as well as post-brain scans) will be sufficient to perform random effect analysis for fMRI BOLD changes with multiple comparison correction using random field theory-based family-wise error correction to control for multiple comparison (http://www.fil.ion.ucl.ac.uk/spm/).

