#### Primary outcome measures

Key measures include opioid abstinence confirmed by negative urine screening and self-report, levels of pain measured by BPI, the intensity of craving tracked by OCS, beta-endorphin levels, and fMRI-BOLD responses to tasks (stop signal, visual cue craving) and resting state functional connectivity through fMRI.

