### Data analysis

The R programming language will be used to analyze data (R Core Team 2022; 56). Details of dropped-out/withdrawn patients will be recorded. Missing data, drop-outs, non-compliance, and adverse events will be managed in collaboration with the biostatistician and supervisor. The data of all randomized participants will be analyzed using intent-to-treat analysis and mixed model multivariate analysis. Imaging analysis details are provided below. OST/MOUD dosage will be used as a covariate in the analysis. Interim analysis will be done when 50% of the target sample size completes the trial. Information regarding solicited and spontaneously reported adverse events and other unintended effects of trial interventions or trial conduct will be documented and reported to the DMC as well as the ethics committee of the institution. The DMC will have access to interim analysis results and will take the decision to terminate the trial in case of unreasonable morbidities or mortalities among the recruited participants during the trial. Information obtained from the interim analysis may be used for enhancing trial efficiency by updating design and/or sample size adjustments, this will be done as per the suggestions of DMC and after due approval from the funding agency. Trial conduct will be audited once in a year by the DMC, the process will be independent from investigators and the sponsor.

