**Physiological Measures**				
Plasma Beta-Endorphin Levels	✓		✓	✓
Functional Magnetic Resonance Imaging (visual cue craving task, stop signal task, resting state functional connectivity and MRS)	✓		✓	✓
Heart Rate Variability	✓	✓		
Pressure Algometer (Pain Threshold)	✓	✓	✓	✓
Serum Cortisol	✓		✓	✓

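### The task-fMRI group model treats the pre-randomisation scan as an outcome level and does not adjust for it, which gives away precision at no benefit

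*Protocol article*

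**What the plan says.** The section Data Preprocessing and Analysis fixes the imaging model. Subject-level contrast estimates "will subsequently be transferred to the group level via the AFNI program 3dLME". There, "The group will be modelled as a between-subject factor with two levels (TAU and YAT"), and "time (0, 3, and 6 months) will be treated as a within-subject variable and participants as random factors".

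The fMRI row of Table 1 is ticked at day 0, three months and six months, so time 0 is the scan taken before the intervention starts. The Data analysis section names one covariate: "OST/MOUD dosage will be used as a covariate in the analysis". Neither section mentions the baseline value of the outcome as a covariate, or a common baseline mean for the two arms.

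The Primary outcome measures section lists "fMRI-BOLD responses to tasks (stop signal, visual cue craving) and resting state functional connectivity through fMRI". The imaging sample is stated under Sample size estimation: "The subset sample size of 50 for imaging studies (in each group", with scans before and after). Trial design gives a "parallel group superiority trial with a 1:1 allocation ratio".

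**The concern.** In a randomised trial the two arms share the same expected baseline. A model with group and time as crossed factors, and no constraint at time 0, estimates a separate baseline mean for each arm and then subtracts that estimate from the follow-up difference. The chance baseline difference is subtracted in full, however weakly baseline predicts follow-up. Adjustment subtracts only the part that baseline predicts.

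What is at stake is precision on two primary outcomes whose sample is a subset of the trial and whose inference already carries a family-wise error correction. The baseline scan is collected anyway, so the choice of model decides how much it is worth.

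The text also leaves open whether the group-by-time term or the group main effect carries the treatment effect. The second would include an occasion at which no treatment effect can exist.

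**Working it through.** **The plan's own figure.** The 50 per group cannot be reproduced. The article gives no effect size, standard deviation, power or correlation for the imaging subset.

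**Inputs.** From the documents: n = 50 per group, 1:1 allocation, scans at 0, 3 and 6 months. Assumed: outcome SD of 1 at each time, complete data, free baseline means by arm, and r (baseline to 6 months) ranged because the documents do not give it.

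**Step 1: variance under the plan.** With free means in each group-by-time cell and complete data, the 6-month group-by-time contrast equals the between-arm difference in change from baseline:

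Var(plan) = (2/n) × 2(1 − r)

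**Step 2: variance with baseline used.** With baseline as a covariate, or with arm means constrained equal at time 0:

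Var(adjusted) = (2/n) × (1 − r²)

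**Step 3: ratio.** (1 − r²) / [2(1 − r)] = (1 + r)/2. This is below 1 for every r below 1 and does not depend on n.

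**Step 4: numbers.** With 2/n = 0.04:

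| r | SE, plan | SE, adjusted | Variance ratio | 50 per arm under the plan is worth |
|---|---|---|---|---|
| 0.3 | √(0.04 × 1.4) = 0.237 | √(0.04 × 0.91) = 0.191 | 0.65 | 32.5 |
| 0.5 | √(0.04 × 1.0) = 0.200 | √(0.04 × 0.75) = 0.173 | 0.75 | 37.5 |
| 0.7 | √(0.04 × 0.6) = 0.155 | √(0.04 × 0.51) = 0.143 | 0.85 | 42.5 |
| 0.9 | √(0.04 × 0.2) = 0.089 | √(0.04 × 0.19) = 0.087 | 0.95 | 47.5 |

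The last column is 50 × (1 + r)/2.

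**Step 5: comparison with ignoring baseline.** Comparing the 6-month scans alone has variance 2/n, an SE of 0.200. The planned contrast is less precise than that whenever 2(1 − r) > 1, that is, when r < 0.5.

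**Step 6: check on the covariance structure.** A generalised least squares calculation with all three occasions gave the same SEs under compound symmetry. Under a first-order autoregressive structure with lag-one correlation 0.5, r over two intervals is 0.25. The ratio is then 1.25/2 = 0.625, which means the planned variance is 1.60 times the adjusted one.

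**Step 7: if the group main effect were the test.** For a constant effect δ at 3 and 6 months, the average over the three occasions is (0 + δ + δ)/3 = 2δ/3.

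**Power, for illustration only.** For one voxel or region, an assumed effect of 0.5 SD and two-sided alpha 0.01, power is 32% under the plan and 52% adjusted at r = 0.3, 47% and 62% at r = 0.5, and 74% and 82% at r = 0.7. At r = 0.9 both are 99.9%. These are not the power of the planned cluster-level test.

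**The case against.** **The model is valid.** A group-by-time mixed model with baseline as one occasion is common and, under randomisation, unbiased. That stands. A reader might infer that the imaging results would be biased or invalid; nothing in the document supports that.

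**Part of the reading rests on silence.** The article lists factors, not a full formula, and a baseline-constrained model would also have group and three times. This is fair, but a constraint at time 0 is a deliberate departure from two crossed factors, and the article states none. The free-means reading is the natural one.

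**Scope.** A reader might take all three fMRI primary outcomes to be affected. The 3dLME sentence concerns condition contrasts from the subject-level fit, which are the stop-signal and cue tasks. Resting-state data go through independent component analysis in GIFT, and their group model is not clearly described. A reader might also call imaging the smallest sample in the trial. That is unsupported, because spectroscopy is done in a small subset of unstated size.

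**Size.** The gain depends on an unknown r and is slight when r is high. The alpha of 0.01 belongs to the overall sample size statement, while imaging inference uses cluster-level family-wise thresholds. Both points stand, so the variance ratio is the result and the power figures are only an illustration.

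**Main effect.** The article does not say that a group main effect will be tested. Its stated aim for the cue task, to quantify change after the intervention, points to group-by-time. The shrinkage to two-thirds is therefore conditional.

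**Conclusion.** The point holds as one of efficiency, not validity, for the two task-fMRI primary outcomes. As written, the model has higher variance for the 6-month effect than a baseline-adjusted one at every r below 1. The excess is 1/0.65 − 1 = 54% at r = 0.3, 33% at r = 0.5, 18% at r = 0.7 and 5% at r = 0.9. Below r = 0.5 the planned contrast does worse than discarding the baseline scan.

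This rests on free baseline means by arm, equal variances and complete data. The direction is certain on those terms. The size is not, because the documents give no r. No specific loss of power can be claimed for the cluster-corrected test.

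**What to change.** Take one of two routes for the task contrasts:

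1. Model the 3- and 6-month contrast estimates as responses, with each patient's baseline contrast value as a voxel-wise or region-of-interest covariate.
2. Keep all three times as responses but constrain the two arms to a common mean at time 0. This also keeps patients who have a baseline scan and miss a follow-up scan.

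In either case, state that the test is the group difference at 6 months, so that the group main effect over all three times is not used. If the resting-state group comparison uses the same model, treat it the same way.

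This is a free improvement: only the model specification changes, with no added scan, visit or patient. The Ethical statement section counts changes to analyses among the major amendments to be communicated, so the change needs that notice. It should be made before any unblinded imaging data are seen.

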### Hypothesis

The yoga-based intervention will serve as a useful adjunct therapy to standard treatment as compared to standard treatment alone in patients with OUD by:

**Primary**-1) improving opioid abstinence, 2) reducing pain and craving, 3) enhancing plasma beta-endorphin levels, and 4) reducing reward system activation in response to visual cue craving paradigm, increasing activation in response to the cognitive control task (stop signal), and increasing coherence in resting state functional connectivity through fMRI.

**Secondary**-1) reducing withdrawal symptoms, disease severity, stress, anxiety, sympathetic arousal as measured by HRV, serum cortisol levels, enhanced brain GABA levels through MRS, cognitive performance (n-back task, Stroop task), reducing dosage and side effects of buprenorphine, and improving sleep quality, pain threshold, and yoga-based mental attitude (*guna profile-sattva, rajas, tamas*).

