#### Predictions on mechanisms of action

We hypothesize that yoga will act through reversing the excitatory/ inhibitory imbalance in the CNS, by increasing GABA and parasympathetic activity, and reducing allostatic load (by reducing cortisol and enhancing beta-endorphins). It will also act by enhancing cognition (enhancing response inhibition with associated activation of prefrontal and anterior cingulate cortices during the stop signal task and improving cognitive performance as measured by n-back task and Stroop task) and by reducing craving as demonstrated by clinical assessments and reducing activation of brain regions that are known to be activated in patients with addiction in response to addiction-related visual cues (prefrontal and orbitofrontal regions, cingulate cortices, inferior frontal regions, limbic system including amygdala and ventral striatum including nucleus accumbens). Yoga may also act by improving functional resting brain connectivity and coherence and enhancing grey matter volume in this population.

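### The primary reward-system hypothesis for the cue task has no matching regional test, and the planned cluster-extent rule is weak for the small structures named in advance

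*Protocol article*

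**What the plan says.** Under Primary outcome measures, the BOLD response to the visual cue task is one of the primary outcomes. The primary hypothesis for it is regional and directional: "reducing reward system activation in response to visual cue craving paradigm". Predictions on mechanisms of action lists where the reduction is expected. Some of the regions are large ("prefrontal and orbitofrontal regions, cingulate cortices, inferior frontal regions") and some are small ("limbic system including amygdala and ventral striatum including nucleus accumbens").

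Data Preprocessing and Analysis fixes the contrast ("our primary interest lies in the drug-neutral cue contrast") and a voxelwise 3dLME model with group and time. On multiplicity it says: "A cluster-level family-wise error (FWE) rate corrected significance threshold will be computed to correct for multiple comparisons". The threshold comes from 3dClustSim, with residual smoothness "estimated with the -acf option inside the gray matter mask using the 3dFWHMx tool". Then: "The thresholds derived will subsequently be applied to the statistical maps produced by 3dLME, aiding in the identification of significant clusters".

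Neither this section nor Sample size estimation mentions a region of interest, a small-volume correction or a regional summary measure. Sample size estimation also names a different correction, based on random field theory with a link to the SPM site. It calls 50 per group sufficient for imaging without an effect size, alpha or power.

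**The concern.** The hypothesis is about named structures, but the stated test does not use those names. Two things follow.

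- A cluster-extent threshold declares an effect only where enough contiguous voxels exceed the cluster-forming level. A structure about as small as the critical cluster has little chance of passing at a medium effect, however real the effect. A null map would then say little about the amygdala or nucleus accumbens, which are central to the reward-circuit claim.
- No rule says which significant cluster would count as support for the primary hypothesis. That choice would be made after the map is seen.

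**Working it through.** **Inputs in the protocol.** 50 per group with pre and post scans; a medium effect with no number; 6 mm smoothing; in-plane voxel 192/64 = 3 mm; two-tailed alpha 0.01 for the trial as a whole.

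**Not stated, so assumed.** d = 0.5 (0.8 as an upper case); cluster FWE 5%; two-sided cluster-forming p of 0.01 or 0.001; residual smoothness 7, 9 or 11 mm; search volume 700 ml; 3 mm isotropic voxels (0.027 ml); single spherical regions with a uniform effect.

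**Step 1: the plan's own figure.** The 50 per group cannot be reproduced, because no inputs are given for it.

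**Step 2: shift of the voxel statistic.** d × √(n/2) = 0.5 × √25 = 2.5. The cluster-forming thresholds are 2.576 (p < 0.01) and 3.291 (p < 0.001). The expected share of affected voxels that pass is Φ(2.5 − 2.576) = 0.47 and Φ(2.5 − 3.291) = 0.21.

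**Step 3: critical cluster, simulated under the null.**
- p < 0.001: 13, 21 and 32 voxels at 7, 9 and 11 mm, which is 0.35, 0.57 and 0.86 ml.
- p < 0.01: 33, 64 and 93 voxels, which is 0.89, 1.73 and 2.51 ml.

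A region of 19 voxels (0.51 ml) is expected to supply 0.51 × 0.47 = 0.24 ml or 0.51 × 0.21 = 0.11 ml above threshold, well short of either range. A region of 587 voxels (15.8 ml) supplies 15.8 × 0.47 = 7.4 ml or 15.8 × 0.21 = 3.3 ml, well above both.

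**Step 4: simulated power of the cluster rule, 50 per group, range over 7-11 mm.**

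| Region | d = 0.5, p < 0.001 | d = 0.5, p < 0.01 | d = 0.8, p < 0.001 | d = 0.8, p < 0.01 |
|---|---|---|---|---|
| 0.5 ml (accumbens-sized) | 0-10% | 0-1% | 0-71% | 0% |
| 1.5 ml (amygdala-sized) | 8-36% | 1-38% | 81-97% | 3-98% |
| 2.5 ml (ventral-striatum-sized) | 22-53% | 5-66% | 93-100% | 48-100% |
| 16 ml (frontal or cingulate patch) | 86-100% | 96-100% | 100% | 100% |

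Each cell uses 400 replicates. Cells where the region is about as large as the critical cluster are unstable. The 48% is one: 93 voxels in the region against a critical size of 93.

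A separate simulation used 3 × 3 × 3.75 mm voxels, a mask of about 770 ml, 8 or 10 mm smoothness and p < 0.001 or 0.005. At d = 0.5 it gave 0-6% at 0.5 ml, 5-27% at 1.4 ml, 36-68% at 3.1 ml and 66-91% at 7 ml.

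**Step 5: region-mean test at a region-mean d of 0.5.** Two-sample t, 98 degrees of freedom, non-centrality 0.5 × √25 = 2.5.

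| Two-sided level | Power |
|---|---|
| 0.05, one mask | 70% |
| 0.05/2 = 0.025 | 59% |
| 0.05/3 = 0.0167 | 53% |
| 0.05/7 = 0.0071 | 41% |
| 0.01, one mask | 45% |
| 0.01/2 = 0.005 | 36% |
| 0.01/3 = 0.0033 | 31% |

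The two effect definitions differ: Step 4 sets d at each voxel and Step 5 sets it for the regional average. A uniform voxelwise d of 0.5 implies a larger region-mean effect, because averaging removes noise. Setting 53-59% beside 0-38% therefore does not flatter the regional test.

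**The case against.** The strongest reply is that this is a condensed article. An analysis plan may exist that defines masks, the cluster-forming p and the FWE level, and cluster FWE is a valid form of error control. That stands in part: such a plan could settle the matter, and nothing in the article forbids a regional analysis. But the article goes well beyond a summary. It fixes the software, model, factors, smoothness estimator and correction, and the test so fixed does not address the primary hypothesis region by region.

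Four stronger readings are tempting and are not supported:

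- **That the search is stated to cover the whole grey matter.** The grey-matter mask is tied to the smoothness estimate; the mask for the cluster simulation is not given. What can be said is that nothing limits it to the listed regions.
- **That the analysis can neither confirm nor refute the hypothesis.** A significant cluster has a location, so a finding in a reward region is possible. No sentence says that a cluster anywhere counts as success, so power for a region elsewhere is not a false-confirmation rate.
- **That the whole outcome is underpowered.** The list also names large frontal and cingulate regions, where the planned rule works.
- **That a regional test would have 83-100% power.** Those figures need one uncorrected mask that matches the effect exactly. Corrected power is far lower, and at about seven masks it falls to 41%.

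**Conclusion.** The concern holds in a limited form. The primary cue-reactivity hypothesis names a system and its regions, and the only inference the article states is a cluster-extent map with no region-restricted test. At a medium effect with 50 per group, that rule is weak for the smallest named structures and adequate for effects that fill large frontal or cingulate regions.

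The absence of a regional test is read directly from the text. The size of the loss is not: it depends on smoothness, cluster-forming p, search volume, region volumes and effect size, none of which the protocol gives as needed. At d = 0.8 with p < 0.001, most of the loss disappears for an amygdala-sized region but not reliably for an accumbens-sized one. The threshold is not the only limit on power either: one regional test at the trial's alpha of 0.01 has only about 45% at d = 0.5. This is a cheap improvement worth making, not a flaw that invalidates the imaging analysis.

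**What to change.** In Data Preprocessing and Analysis, before unblinding:

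1. Define the primary test of the reward-system hypothesis as the between-arm difference in change of the drug-neutral contrast, averaged within a small set of anatomical masks in the template space for the amygdala and the ventral striatum/nucleus accumbens, with correction across those masks. Two or three masks is the useful number. Whole-mask averages over prefrontal cortex, or one cluster search over the union of all listed regions, would gain little.
2. Keep the cluster-corrected map for the large frontal and cingulate regions and for findings elsewhere. State that only clusters inside the listed regions count as support for the hypothesis.
3. Reconcile the random-field correction in Sample size estimation with the 3dClustSim correction in the analysis section.

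The cost is wording and mask definition; no extra scans are needed. Findings outside the named regions become exploratory. Power after correction stays moderate: 53-59% at a family level of 0.05, and about 45% for one mask at 0.01 (31-36% if 0.01 is itself split over two or three masks).
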